### Intervention

2.5

#### Basic intervention

2.5.1

The study was based on all patients receiving Routine Standard Postoperative Care (RSPC) according to the ERAS consensus and the Chinese Pathway Management Guidelines (2018).

#### Intervention of EA group

2.5.2

Provide EA treatment on the basis of comprehensive intervention. According to the “WHO Standard acupuncture point locations in the Western Pacific Region”.

##### Bilateral Zusanli (St36)

2.5.2.1

On the anterior aspect of the leg, on the line connecting ST35 and ST41, 3 B-cun inferior to ST35.

##### Bilateral Neiguan (Pc6)

2.5.2.2

On the anterior side of the forearm, between the tendons of the palmaris longus and the flexor carpi radialis, 2 B-cun proximal to the palmar wrist crease.

##### Procedure

2.5.2.3

All patients are placed in a supine position and the acupoints are routinely disinfected. The 40 mm disposable sterile acupuncture needle (Hwato, Suzhou, China) was used. The needle was directly punctured 0.5∼1 cun (about 15–30 mm). The acupuncture manipulation is reinforcing and reducing to DeQi. The patient may not be fully awakened at the time of the first acupuncture, so we defined DeQi as the sensation of blockage felt by the acupuncturist during the maneuver. After, use an electric wire to connect both sides of ST36, using a continuous wave type with a frequency of 2 Hz and an intensity of 2–3 mA. There were two times of EA interventions, with the first intervention starting after the surgery, and the second intervention lasting 30 min on the morning of the second postoperative day. When taking the needle, gently press with your hand and use a clean cotton pad to prevent bleeding.

#### Intervention of EA-sham group

2.5.3

We defined EA-sham as electroacupuncture at non-meridian and non-acupoint locations. Consistent with the intervention in the EA meridian acupoint group mentioned above, acupoint selection intervention was performed by opening approximately 1.5 cm next to the ST36 and PC6.

### Outcomes

2.6

#### Main outcomes

2.6.1

The primary outcomes are postoperative abdominal distension grading and postoperative abdominal distension VAS score.
1.Postoperative abdominal distension grading: Postoperative abdominal distension is divided into four levels: Grade 0 (score 0): no sense of distension; Grade 1 (score 1): mild distension, slight increase in abdominal wall tension, does not affect rest and sleep; Grade 2 (score 2): moderate distension, high abdominal wall tension, affects rest and sleep; Grade 3 (score 3): severe distension, high abdominal wall tension, unable to rest and sleep. The degree of distension is observed and recorded every hour for 1–6 h and 24 h postoperatively.2.Postoperative abdominal distension VAS score: Postoperative abdominal distension, pain, and nausea will be assessed using the VAS method, with the degree of distension observed and recorded every hour for 1–6 h and 24 h postoperatively.

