#### Secondary outcomes

2.6.2

Secondary outcomes include the time for postoperative abdominal distension to disappear, length of hospital stay, postoperative pain, nausea and vomiting, time to first independent walking, time to first postoperative flatus, time to first postoperative defecation, postoperative complications, and other qualitative indicators for patients.
1.Time for postoperative abdominal distension to disappear: Refers to the difference between the time for postoperative abdominal distension to disappear and the end of the surgery. Patients and their family members should be carefully informed to observe and report the time when the postoperative abdominal distension sensation disappears, and the details should be recorded in the Case Report Form (CRF).2.Postoperative pain, nausea, and vomiting: Postoperative pain and nausea will be assessed using the Visual Analog Scale (VAS). The degree of pain and nausea will be observed and recorded every hour from 1 to 6 h postoperatively and at 24 h, and the frequency of vomiting will be recorded.3.Time to first postoperative flatus: Refers to the difference between the time of the first postoperative flatus and the end of the surgery. Patients and their family members should be carefully informed to observe and report the time of the first postoperative flatus, and the details should be recorded in the CRF.4.Time to first postoperative defecation: Refers to the difference between the time of the first postoperative defecation and the end of the surgery. Patients and their family members should be carefully informed to observe and report the time of the first postoperative defecation, and the details should be recorded in the CRF.5.Length of hospital stay: The time from the end of the surgery to discharge.6.Postoperative complications: Other postoperative complications will be recorded in the CRF.7.Other qualitative indicators for patients.

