### Statistical analysis

2.8

All statistical analyses will be conducted according to the intention-to-treat (ITT) principle, which includes patients who have received at least one session of EA treatment. All paper-based data will be electronically entered and analyzed using SPSS 26.0 (per-protocol set for robustness analysis of the results). In the statistical description, continuous data will be presented as mean ± standard deviation (M ± SD) or median and interquartile range, while categorical data will be presented as frequencies and percentages. Demographic and other baseline data will be compared using ANOVA and chi-square tests. Kaplan–Meier analysis will be used for key times of primary outcomes and secondary endpoints, and group comparisons will be made using the Breslow (generalized Wilcoxon) test. Differences in the incidence rates of nausea, vomiting, and abdominal distension will be compared using chi-square tests or the Mann–Whitney U test. The occurrence rates and severity of compliance will be analyzed using chi-square tests or the Mann–Whitney U test at a significance level of *α* = 0.05. Missing data will be handled using last observation carried forward and multiple imputation.

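### Two co-equal primary outcomes, each recorded at seven times, have no named deciding contrast, so a superiority claim could rest on whichever comparison turns out favourable

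*Protocol article*

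**What the plan says.** Section 2.6.1 (Main outcomes) opens: "The primary outcomes are postoperative abdominal distension grading and postoperative abdominal distension VAS score". For the grade (0 to 3) it adds: "The degree of distension is observed and recorded every hour for 1–6 h and 24 h postoperatively". The VAS item has the same schedule, "with the degree of distension observed and recorded every hour for 1–6 h and 24 h postoperatively". That is seven readings per outcome. The section ranks neither outcome above the other. It gives no deciding time or summary over time, and no rule on whether success needs one outcome or both.

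Section 2.8 (Statistical analysis) touches the primary outcomes in two places. One is "Kaplan–Meier analysis will be used for key times of primary outcomes and secondary endpoints", with group comparison by the Breslow test. The other is "Differences in the incidence rates of nausea, vomiting, and abdominal distension will be compared using chi-square tests or the Mann–Whitney U test". The only significance level in the article, "at a significance level of *α* = 0.05", closes a sentence about compliance.

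On purpose, section 2.1 describes a superiority design with a directional hypothesis, and the Abstract (Expected outcome) repeats that hypothesis. Section 2.7 calls the study a pilot whose results will help to size a later trial.

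The VAS item in section 2.6.1 also says "Postoperative abdominal distension, pain, and nausea will be assessed using the VAS method", although section 2.6.2 lists pain and nausea as secondary outcomes.

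**The concern.** A superiority claim needs a defined comparison on which it stands or falls. Here the reader cannot tell in advance which result would count. Grade at 3 h, VAS at 24 h, a mean over the day and the presence of distension at some hour are all compatible with the text.

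Two things are at stake. First, if any favourable contrast may be called primary, 0.05 is not the error rate of the superiority claim, and a mixed pattern across scales or hours has no agreed reading. Second, the pilot is meant to inform the next sample size. Without a named contrast there is no defined effect or standard deviation to carry forward, and a contrast chosen because it looked best will overstate the effect.

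**Working it through.** **Inputs from the protocol article**

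- Primary outcomes: 2 (section 2.6.1).
- Scheduled times per outcome: 1, 2, 3, 4, 5, 6 and 24 h, so 7 (section 2.6.1). Largest set of hourly contrasts: 2 × 7 = 14.
- Level: 0.05, the only one stated (section 2.8). Sidedness is not stated; two-sided is assumed.
- Correlations between test statistics: not given, so every value below is an assumption.

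**The plan's own figure.** The article states no family-wise error rate or power. Its one derived figure is the sample size of 72 (section 2.7). Reading 30 as per arm, 30 × 1.20 = 36, and 36 × 2 = 72, which reproduces it. No effect size or named contrast enters this figure, so it does not reveal which comparison was meant to decide the trial.

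**Independent tests.** The chance of at least one false positive among k tests is 1 − (1 − 0.05)^k.

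- k = 2: 1 − 0.95² = 9.75%
- k = 7: 1 − 0.95⁷ = 30.2%
- k = 14: 1 − 0.95¹⁴ = 51.2%

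**Correlated tests.** Repeated ratings of one symptom in the same patient are correlated, so the independent case is a ceiling. The chance that at least one |Z| exceeds 1.96 with no true effect was simulated from correlated normal statistics (400,000 draws), using one common correlation:

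| Correlation | 2 contrasts | 7 contrasts | 14 contrasts |
|---|---|---|---|
| 0.3 | 9.5% | 27.0% | 43.8% |
| 0.5 | 9.0% | 23.0% | 34.8% |
| 0.7 | 8.3% | 17.9% | 24.8% |
| 0.9 | 7.0% | 11.4% | 14.1% |
| 0.95 | 6.5% | 9.2% | 10.8% |

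A second structure let correlation decay over the seven readings (AR(1), each reading one step from the next, 200,000 draws). With 0.7 between adjacent readings and 0.5 between scales, 14 contrasts give 37.5%. With 0.95 and 0.9 they give 15.7%. For common correlations of 0.5 or more and for the decaying structures, the range is therefore about 11–38%.

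**Dependence on the success rule.** If each outcome is reduced to one contrast and either may succeed, the error is about 7–10%. If both must succeed on one named contrast each at 0.05, there is no inflation. The article does not choose between these rules.

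**Do the analyses in section 2.8 settle it?** Neither primary outcome is a time to an event; the time until distension disappears is secondary in section 2.6.2. The key times in the Kaplan–Meier sentence are not defined. The incidence comparison names no hour or summary, and leaves a choice between two tests.

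**The case against.** The strongest reply is that section 2.6.1 sets a recording schedule, not a testing schedule. Nothing in section 2.8 says that groups will be compared hour by hour, and a Breslow comparison gives one test per time variable. The 0.05 stands in the compliance sentence, and silence on adjustment is not proof that none is planned: an unseen analysis plan may hold it. The trial is also declared a pilot with no power claim, so family-wise error matters less.

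Most of this stands, and it limits the size of the point. The 14 comparisons are an inference, the absence of an adjustment method is not itself a finding, and the pilot label lowers the severity. What remains is the choice of the primary contrast. That belongs where the primary outcomes are defined, and section 2.6.1 leaves it open. The pilot label does not remove this, because the superiority hypothesis is stated twice and because the next trial's sample size needs one defined effect.

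A reader might also infer from the mention of pain and nausea in the VAS item that there are four primary outcomes and 28 comparisons. The document does not support that. The section's opening sentence and the item's title limit the primaries to distension, the timing clause refers only to distension, and section 2.6.2 places pain and nausea among the secondary outcomes. It is a wording overlap.

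**Conclusion.** The point holds as a gap in the definition of the primary outcome: two equal outcomes, seven times each, and no deciding contrast, set against a stated superiority hypothesis. The false-positive chance is about 7–10% with one contrast per outcome where either may succeed. It is about 11–38% if all 14 scheduled contrasts are tested and any may succeed. These figures assume two-sided tests at 0.05 and correlations that the article does not supply; at a common correlation of 0.3 the 14-contrast figure would be 43.8%.

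A reader might take 51% as the trial's error rate. It is only the ceiling under independence, which is implausible for two ratings of the same symptom in the same patients. Nor does the article commit itself to 14 unadjusted tests; it simply does not exclude them. Given the pilot status, this should be fixed, but it is not a must-fix defect.

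**What to change.** Before any unblinded analysis, amend sections 2.6.1 and 2.8 as follows.

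1. Name one primary contrast, for example the between-group difference in distension VAS over the scheduled times from a single repeated-measures model, tested once at two-sided 0.05. One pre-named time would serve as well.
2. Test distension grade next, on one named contrast, only if the VAS contrast is significant. This ordering keeps the overall error at 5%. If both outcomes are to stay co-equal, 0.025 for one contrast each also holds it to at most 5%.
3. Report hourly differences on both scales descriptively with 95% confidence intervals.
4. Remove pain and nausea from the primary VAS item.

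The cost is wording and a registry update; no new data or patients are needed. The downside is that an isolated hourly difference can no longer be claimed as primary. An equal-weight mean also gives the first six hours 6/7 of the weight and 24 h only 1/7, which matters if the effect is expected late; in that case a named time or other weights may suit better. Averaging has some gain in precision: under equal correlation ρ between times, the variance of a seven-reading mean is (1 + 6ρ)/7 of a single reading's, or 0.66 at ρ = 0.6 and 0.83 at ρ = 0.8. That gain can be lost if the effect varies over time.

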During the LC procedure, nitrogen or carbon dioxide is injected into the abdominal cavity for visualization of the internal organs (6). These gases need to be expelled from the body after the surgery, but sometimes they may remain in the abdominal cavity. As a result, abdominal distension and other gastrointestinal dysfunctions caused by pneumoperitoneum and various factors are common complications after LC (7, 8). According to an early study (9), 80% of patients with gallstones who underwent cholecystectomy experienced severe digestive disorders, suggesting that gallbladder inflammation may be a contributing factor to gastric bloating-related digestive disorders. Additionally, due to pneumoperitoneum, surgical trauma, and the effects of anesthesia, normal bowel movements often fail to recover within 24 h after the surgery. Furthermore, severe abdominal distension may impede venous blood flow in the inferior vena cava, leading to complications such as deep vein thrombosis (10). Therefore, improving abdominal distension, pain, and other gastrointestinal dysfunction after LC surgery plays an important role in promoting patient recovery and improving postoperative quality of life.

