### Design

2.1

This study is a single-center, randomized controlled clinical trial. The study aims to evaluate the clinical efficacy and efficiency of EA in treating post-laparoscopic cholecystectomy bloating. This study is designed as a superiority trial, hypothesizing that the efficacy of EA at meridian acupoints is superior to sham EA in the integrative medical care after laparoscopic cholecystectomy. The protocol of this clinical trail is based on or refers to the following standard items: the Standard Protocol Items: Recommendations for Interventional Trials (SPIRIT) checklist (19) and its TCM extension (20); Consolidated Standards of Reporting Trials (CONSORT) (21); Standards for Reporting Interventions in Clinical Trials of Acupuncture (STRICTA) (22); WHO standard acupuncture point locations in the Western Pacific region. This clinical trial protocol is approved by the Ethics Committee of Putuo District Central Hospital, Shanghai (approval number: PTEC-A-2023-29-1) and registered with the Chinese Clinical Trial Registry (Registration number: ChiCTR2300073134).

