### Patient recruitment

2.2

This study is expected to include patients who undergo LC at the Department of General Surgery, Putuo Hospital, Shanghai University of Traditional Chinese Medicine, from July 1, 2023 to December 31, 2024. Patients who express interest will be recruited through preoperative interviews and pre-screening. After confirmation by clinical physicians and signing an informed consent form, baseline data will be collected. The criteria for pre-screening were defined as Patients with benign gallbladder diseases requiring LC as outlined in the “Expert Consensus on Surgical Treatment of Benign Gallbladder Diseases in China (2021)” (23) (Figure 1).

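### No preoperative distension rating is named for either primary outcome and only unadjusted tests are stated, which costs precision and leaves any chance imbalance in existing bloating uncorrected

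*Protocol article*

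**What the plan says.** Section 2.6.1 names two primary outcomes: "The primary outcomes are postoperative abdominal distension grading and postoperative abdominal distension VAS score". For the grade (0 to 3) the schedule is: "The degree of distension is observed and recorded every hour for 1–6 h and 24 h postoperatively". For the VAS it is the same: "with the degree of distension observed and recorded every hour for 1–6 h and 24 h postoperatively". The Method paragraph of the abstract repeats these times. All seven ratings fall after surgery.

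The aim in section 2.1 is specific to distension that follows the operation: "The study aims to evaluate the clinical efficacy and efficiency of EA in treating post-laparoscopic cholecystectomy bloating". The Background reports an early study in gallstone patients, "suggesting that gallbladder inflammation may be a contributing factor to gastric bloating-related digestive disorders". The inclusion and exclusion criteria (2.3.1 and 2.3.2) do not mention bloating before surgery.

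A preoperative data point exists. Section 2.2 says: "After confirmation by clinical physicians and signing an informed consent form, baseline data will be collected". Its items are not listed. Section 2.8 gives baseline data one use: "Demographic and other baseline data will be compared using ANOVA and chi-square tests". The tests it names for outcomes are chi-square, Mann–Whitney and Breslow, none of which adjusts for a covariate.

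**The concern.** The trial asks about distension after cholecystectomy, but a score taken only afterwards records total distension. A patient with VAS 4 before and 4 after surgery counts the same as one with 0 before and 4 after. The population has gallbladder disease, which the article itself treats as a possible source of bloating, so some patients may arrive already bloated.

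Two things are at stake. Stable differences between patients add variance to both primary outcomes that a baseline covariate could remove. And if the arms differ by chance in existing bloating, the analysis as described neither shows it on these scales nor corrects for it. There is also a consequence for the next study. Section 2.7 says this pilot will inform a later sample size, but without a preoperative rating it cannot supply the pre/post correlation or the adjusted standard deviation that such a calculation would use.

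**Working it through.** **Inputs from the article (2.7 and abstract).** 30 patients, read as per group; 20% dropout; 72 in total, 36 per group. Significance level 0.05 (2.8), taken as two-sided.

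**Stated figure.** 30 × 1.2 = 36 per group, and 2 × 36 = 72. The total reproduces, so 30 and 36 per arm are used below as the range.

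**Assumptions, because the article gives no value.** Correlation ρ between preoperative and postoperative distension: 0.2 to 0.6. Effect for illustration: 0.5 SD.

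**1. Precision gained by adjustment.** The variance of the adjusted difference is multiplied by 1 − ρ², and the standard error by √(1 − ρ²). The equivalent sample size factor is 1/(1 − ρ²). Power is Φ(0.5 / [√(2/30) × √(1 − ρ²)] − 1.96). The loss of one of 58 degrees of freedom is ignored.

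| ρ | 1 − ρ² | Cut in standard error | Equivalent extra patients | Power at 0.5 SD, 30 per arm |
|---|---|---|---|---|
| 0 (unadjusted) | 1.00 | 0% | 0% | 49% |
| 0.2 | 0.96 | 2.0% | 4% | 51% |
| 0.3 | 0.91 | 4.6% | 10% | 53% |
| 0.5 | 0.75 | 13.4% | 33% | 61% |
| 0.6 | 0.64 | 20.0% | 56% | 68% |

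**2. Chance imbalance.** The standardised baseline difference between arms has mean 0 and SD √(2/n).

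| Per arm | SD of imbalance | P(more than 0.25 SD) | P(more than 0.5 SD) |
|---|---|---|---|
| 30 | 0.258 | 33% | 5% |
| 36 | 0.236 | 29% | 3% |

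An imbalance of d shifts the unadjusted outcome difference by ρ × d. For d = 0.25 SD this is 0.2 × 0.25 = 0.05 to 0.6 × 0.25 = 0.15 SD. For d = 0.5 SD it is 0.10 to 0.30 SD. The standard error of the comparison at 30 per arm is 0.258 SD.

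**3. Is the unadjusted comparison biased?** A simulation under no treatment effect (5,000 runs, 30 per arm, a four-level grade correlated 0.5 with baseline on the underlying scale, Mann–Whitney test) rejected in 4.4% of runs at a nominal 5%. The error rate is not inflated.

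**The case against.** **No bias.** Patients are randomised, so existing bloating is equal between arms in expectation, and the unadjusted test already allows for chance imbalance. This stands. A reader might infer that pre-existing bloating distorts the treatment comparison. The documents and the simulation do not support that; what is lost is precision and the means to correct an imbalance that happens to occur.

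**Silence in a condensed article.** Baseline items are unlisted and the CRF is not shown, so a preoperative distension score may exist. This stands in part. It rules out saying that existing bloating cannot be removed. It does not alter the fact that the article sets out the rating times of its primary outcomes explicitly, and that 2.8 uses baseline data only to compare the groups.

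**The Background is hedged.** A reader might take it to say that gallbladder disease causes bloating. It says only that inflammation may contribute. The figure beside it ("80% of patients with gallstones who underwent cholecystectomy experienced severe digestive disorders") concerns digestive disorders in general, with unclear timing relative to surgery. It is no estimate of preoperative bloating and is not used as one here.

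**The gain may be small.** Long-standing biliary bloating and acute gas-related distension may correlate weakly. At ρ = 0.2 the standard error falls by only 2%. This stands, which is why the range starts there.

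**Time to disappearance.** One might go on to redefine this outcome as return to the patient's own preoperative level. That would change a secondary endpoint that 2.6.2 already defines, and the change is debatable. It is not proposed.

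**Conclusion.** The point holds as a matter of efficiency and interpretation. As described, both primary outcomes mix pre-existing and new distension, no preoperative rating is named, and no baseline-adjusted comparison is stated. The comparison remains valid.

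For an assumed correlation of 0.2 to 0.6, the avoidable loss is 2% to 20% of the standard error, equal to 4% to 56% more patients. At 30 per arm, an imbalance above 0.25 SD would arise in about a third of randomisations. At exactly 0.25 SD the shift in the result is 0.05 to 0.15 SD, which is below one standard error. The size rests wholly on a correlation that the article does not give. The change is worth making because it is cheap, uses an existing contact, and lets the pilot estimate that correlation for the larger trial.

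**What to change.** - **Section 2.6.1:** add one preoperative distension VAS and one distension grade at the existing baseline data collection, before allocation is opened. If the CRF already holds these items, say so and use them.
- **Section 2.8:** compare postoperative distension between groups with the preoperative value as covariate, by ANCOVA or a mixed model for the VAS and an ordinal model for the grade.
- **Section 2.6.2:** leave the definition of time to disappearance as it is.

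**Cost.** One VAS mark, one grade, one CRF line and one covariate. Patients already operated on lack the value and would need mean fill or a missing-value indicator, so the gain shrinks with the share already treated.
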